## Abstract

**Background:**

The choice between operative or nonoperative treatment is questioned for
partial articular fractures of the radial head that have at least 2
millimeters of articular step-off on at least one radiograph (defined as
displaced), but less than 2 millimeter of gap between the fragments (defined
as stable) and that are not associated with an elbow dislocation,
interosseous ligament injury, or other fractures. These kinds of fractures
are often classified as Mason type-2 fractures. Retrospective comparative
studies suggest that operative treatment might be better than nonoperative
treatment, but the long-term results of nonoperative treatment are very
good. Most experts agree that problems like reduced range of motion, painful
crepitation, nonunion or bony ankylosis are infrequent with both
nonoperative and operative treatment of an isolated displaced partial
articular fracture of the radial head, but determining which patients will
have problems is difficult. A prospective, randomized comparison would help
minimize bias and determine the balance between operative and nonoperative
risks and benefits.

**Methods/Design:**

The RAMBO trial (Radial Head – Amsterdam – Amphia – Boston
- Others) is an international prospective, randomized, multicenter trial.
The primary objective of this study is to compare patient related outcome
defined by the ‘Disabilities of Arm, Shoulder and Hand (DASH)
score’ twelve months after injury between operative and nonoperative
treated patients. Adult patients with partial articular fractures of the
radial head that comprise at least 1/3^rd^ of the articular
surface, have ≥ 2 millimeters of articular step-off but
less than 2 millimeter of gap between the fragments will be enrolled.
Secondary outcome measures will be the Mayo Elbow Performance Index (MEPI),
the Oxford Elbow Score (OES), pain intensity through the ‘Numeric
Rating Scale’, range of motion (flexion arc and rotational arc),
radiographic appearance of the fracture (heterotopic ossification,
radiocapitellar and ulnohumeral arthrosis, fracture healing, and signs of
implant loosening or breakage) and adverse events (infection, nerve injury,
secondary interventions) after one year.

**Discussion:**

The successful completion of this trial will provide evidence on the best
treatment for stable, displaced, partial articular fractures of the radial
head.

**Trial registration:**

The trial is registered at the Dutch Trial Register: NTR3413.

## Background

In 1953, Mark Mason wrote his landmark paper on the classification of radial head
fractures [1]. Despite several modifications, the classification is still limited with
regards to the description of stability of the fractured fragments. Fracture
stability is potentially important because unstable fractures are typically
associated with other injuries to the elbow or forearm [2-4]. We therefore prefer describing the characteristics of the fracture we
are addressing; stable, displaced, partially articular fractures of the radial
head.

Open reduction and internal fixation (ORIF) of fractures of the radial head became
popular after the advent of implants and techniques for the fixation of small
articular fracture fragments [5-10]. Subsequently, enthusiasm grew with reports of good results on operative
treatment of isolated, displaced, partial articular fractures [7-9,11].

Members of our study group described satisfactory long-term elbow function following
ORIF of these fractures, but with a high complication rate of 44% [12]. A limitation of this study is the fact that many of the screws used were
of a larger diameter than those that would be used today.

A recent meta-analysis by Kaas et al. compared the results of operative and
nonoperative treatment of isolated, displaced, stable, partial articular fractures
of the radial head [13]. Nine retrospective case series describing 224 patients met their
inclusion criteria. Successful treatment was defined as an excellent or good result
according to various performance scores. Nonoperative treatment was successful in
114 of 142 patients (80%) pooled from the studies. Subsequent operative treatment
after failed nonoperative treatment was reported in three patients (2%). Open
reduction and internal fixation was successful in 76 of 82 patients (93%), with
subsequent surgery in four patients (5%). These differences were statistically
significant; however, the authors noted that the level of evidence of the included
studies was too low to support any firm conclusions.

There is currently no consensus as to the optimal treatment of patients with
isolated, displaced, stable, partial articular fractures of the radial head. This
multicenter prospective randomized trial compares DASH scores twelve months after
screw fixation vs. nonoperative treatment and will help to find the balance between
operative and nonoperative risks and benefits.

## Methods

### Study design

The RAMBO trial is a prospective, international multicenter, randomized
controlled trial. Two academic and six teaching hospitals in the Netherlands as
well as a teaching hospital in the United States and a teaching hospital in
Canada will participate.

### Recruitment and consent

All adult patients with partial articular fractures of the radial head that
comprise ≥ 1/3^rd^ of articular surface,
have ≥ 2 millimeters of articular step-off but less than 2
millimeters of gap between the fragments presenting to either the emergency
department or the outpatient departments of the participating hospitals will be
invited to participate in the trial. The fractures are evaluated on standard
anteroposterior (AP) and lateral radiographs with optional Greenspan view. An
additional Computed Tomography (CT)-scan with axial, coronal and sagittal
reconstructions will be made for post-hoc analysis.

The treating surgeon or a member of the study staff will introduce and explain
the trial to the patient and address any questions the patient might have. The
patient will receive a written information form and a consent form. After
receiving informed consent, eligible patients will be randomized. We will use a
block randomization strategy with random blocksize and stratify for
participating country and age of the patients. Age groups will be 18-49 and
≥50 years old. Applicants will be allocated to either operative or
nonoperative treatment using a web-based randomization program. This web-based
program is secure and only members of the study staff have login credentials. It
is not possible to blind surgeons and patients for the allocated treatment.

### Study population

Patients with the following inclusion criteria are eligible for enrollment:

– ≥18 years of age

– Partial articular fractures of the radial head that comprise
at least 1/3^rd^ of the articular surface, have at least 2 millimeter
of articular step-off but less than 2 millimeter of gap between the
fragments

– Diagnosis based on an anteroposterior and lateral radiograph
(with additional Greenspan view if necessary)

A CT-scan will be obtained after enrollment/randomization

– Fracture amenable to screw fixation according to pre-operative
judgment of operating surgeon

– Definitive treatment initiation <10 days after date of
injury.

If any of the following criteria apply, patients will be excluded:

– Polytraumatized patients (ISS >15)

– Other fractures or dislocations of the ipsilateral or the
contralateral upper extremity

– Radial head fracture as part of an elbow dislocation or
associated fractures of the ipsilateral elbow or forearm

– A nondisplaced or comminuted fracture (also know as Mason type
1 or 3)

– Open fracture

– Pathologic fracture

– Previous ipsilateral olecranon/distal humerus/radial head
fracture

– Pre-existent neurological disorders affecting the upper
extremity

Patient unable to follow treatment protocol

– Unfit for general anaesthesia and/or operative management.

### Intervention

Patients that are assigned to nonoperative management will receive a sling for
comfort and are instructed to start active and active-assisted range of motion
exercises after a resting period of 48 hours. Patients that are assigned to ORIF
will be treated by screw fixation of the radial head. The approach as well as
the number and type of screws used is subject to the preference of the treating
surgeon and will be recorded in our study log.

Patients in both cohorts will be given a leaflet containing instructions for
exercises to regain motion. Patients that prefer to do their exercises with
coaching and supervision can work with an occupational or physical therapist or
see their surgeon more frequently.

### Outcome measures

The primary outcome measure is the DASH outcome measure; a validated,
self-reported questionnaire designed to help describe the disability experienced
by people with upper-limb disorders and also to monitor changes in symptoms and
function over time [14-16].The DASH outcome measure is scored in two components: the
disability/symptom section (30 items, scored 1-5) and the optional high
performance Sport/Music or Work section (4 items, scored 1-5). The DASH gives a
score out of 100, in which a higher score indicates greater disability. The DASH
outcome score is validated in both the English and Dutch language.

Secondary outcome measures consist of;

– The Oxford Elbow Score (OES), which reflects both function and
pain following elbow surgery. The OES consists of three domains; pain, function
and social-psychological. Each domain comprises of 4 questions with 5 response
options per question. Each response is scored 0 to 4, with 0 representing
greater severity. Scores for each domain are calculated as the sum of each
individual item score within that domain. These scores are then converted to a
metric score between 0 and 100 (a lower score represents greater severity) [17,18].

– The Mayo Elbow Performance Index (MEPI), which is based on 4
domains (pain, range of motion, stability and elbow function). A total score
between 95 and the maximum 100 points is considered excellent; 80–95 is
good; 60–80 is fair and less than 60 points is poor [19].

– Elbow pain; Pain level will be determined using the Numeric
Rating Scale, an 11–point scale for patient self-reporting of pain

– Active and passive ROM (flexion, extension, pronation,
supination) of both elbow joints will be measured on both sides using a
universal goniometer.

– Crepitance or block to motion will be assessed with elbow and
forearm motion at admission and every follow up visit

– Number of complications (infection, neurovascular compromise,
subsequent or secondary intervention, arthrosis)

– Determining the need for and number of secondary
interventions

– Radiographic appearance of the elbow joint will be evaluated
on the anteroposterior and lateral radiographs at one year. Heterotopic
ossification will be classified as a bone exostosis or as soft tissue
ossification of a ligament, capsule or muscle (“myositis
ossificans”) according the classification scheme of Broberg and Morrey [20]; degenerative changes of the radiocapitellar and ulnohumeral joints
will be classified as grade zero (no change), grade 1 (slight narrowing of the
joint space with small osteophytes), grade 2 (moderate narrowing of the joint
space, osteophytes and subchondral sclerosis), or grade 3 (severe narrowing of
the joint space, large osteophytes, subchondral sclerosis and cystic
deformation). The final radiographs will also be evaluated for fracture healing
and signs of hardware failure or other complications.

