### Study procedures

Clinical assessment will be performed at admission (baseline), three, six months
and one year after treatment initiation. At each follow-up visit the surgeon
will perform a physical examination of both elbows and complete the MEPI and NRS
scores. Simultaneously, the patient will be sent a link to the online,
patient-specific DASH and OES questionnaires: this will be monitored by the
study coordinator. At the two weeks and twelve months follow-up visit an
anteroposterior and lateral radiograph of the elbow will be made. At the last
follow-up visit, an independent and blinded researcher will record any
interventions, complications and physical therapist visits.

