### Sample size calculation

The primary outcome variable will be the DASH, which has a minimal clinically
important difference of 17 for the elbow [16]. Consequently, a 2-sided unpaired T-test with an alpha-level of 0.05,
a beta-level of 0.1, and an allocation ratio of 1, requires 31 patients in each
group to detect an effect size of 0.85. Anticipating a dropout rate of 25%, a
sample size of 39 patients in each arm is required.

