### Statistical analysis

Normality of continuous data will be tested with the Shapiro-Wilk and
Kolmogorov-Smirnov test as well as by inspecting the frequency distributions
(histograms). Homogeneity of variances will be tested using the Levene’s
test. The analysis will be performed on an intention to treat basis. Patients
with protocol violations will remain in follow-up, and data will be recorded.
Data will be analyzed with and without inclusion of patients with a protocol
violation. Descriptive analysis will be performed to report baseline
characteristics in both treatment groups. For continuous data (e.g. age), means
and standard deviations (parametric data) or medians and percentiles
(nonparametric data) will be calculated. For categorical data (e.g. gender)
frequencies will be calculated.

Patients will be analyzed according to the intention-to-treat protocol. The
primary outcome, DASH at one year will be corrected for age and assessed using
an analysis of covariance (ANCOVA). Trends in DASH scores among the different
time points will be assessed using a repeated measures ANOVA if the data is
normally distributed. The secondary outcomes; MEPI, OES, pain as indicated on a
Numerical Rating Scale (NRS), Range of Motion (ROM) will be analyzed in a
similar manner. The radiological outcome, number of conversions and complication
rate will be determined using either a Fisher Exact or a Chi square test,
depending on the order of magnitude of the results.

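### Range of motion is measured on both elbows, but the stated range-of-motion model adjusts for age only and gives the uninjured side no role, which may cost precision on a secondary outcome

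*Protocol article*

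**What the plan says.** All references are to the protocol article.

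- **Outcome measures.** ROM is a secondary outcome: active and passive flexion, extension, pronation and "supination) of both elbow joints will be measured on both sides using a" goniometer. The Abstract names flexion arc and rotational arc as the ROM outcomes.
- **Study procedures.** At each follow-up visit the surgeon "will perform a physical examination of both elbows and complete the MEPI and NRS" scores. A clinical assessment is also scheduled at admission, but the section does not say that it covers both sides.
- **Study population.** Other fractures or dislocations are excluded on the injured side and on the "contralateral upper extremity". The exclusion for earlier elbow fractures is limited to one side: "Previous ipsilateral olecranon/distal humerus/radial head" fracture.
- **Statistical analysis.** The "primary outcome, DASH at one year will be corrected for age and assessed using" ANCOVA. Changes over time are to be examined by repeated measures ANOVA if the data are normally distributed. Among the secondary outcomes, "Numerical Rating Scale (NRS), Range of Motion (ROM) will be analyzed in a" similar way. Age is the only covariate named.
- **Recruitment and consent.** Randomisation is stratified by country and by age group.
- **Discussion.** Surgery is said to offer possibly better ROM, at a possibly higher risk of complications.

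**The concern.** The ROM model is borrowed from the DASH. The DASH has no value from the other arm, but ROM does, and the trial collects it. People differ in their natural elbow and forearm motion, and the uninjured side carries information about each patient's own normal range. With age as the only covariate, that variation stays in the error term.

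The trial is small and was sized on the DASH alone, so precision for ROM was not planned. Leaving the use of the second side open also leaves three analyses available later: the raw arc, the side-to-side difference, and the percentage of the other side.

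**Working it through.** **1. The plan's own figure.** The documents give no sample size, SD or correlation for ROM. The only stated figure is for the DASH: under Sample size calculation, a difference of 17 points (standardised, 0.85) with two-sided alpha 0.05, 90% power and equal arms leads to 31 per arm. The exact noncentral t solution is 30.08, which rounds up to 31 (power 90.9% at 31). The figure reproduces, and the point does not depend on it. It serves only to give realistic numbers analysed: 31 per arm, or 29 per arm if 25% of the planned 39 drop out (39 × 0.75 = 29.25).

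**2. Effect of adding the uninjured arc.** Let ρ be the correlation between the injured-side arc at one year and the uninjured-side arc, given age. It must be taken given age because age is already in the model.

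- Residual variance is multiplied by 1 − ρ².
- The equivalent sample-size multiplier is 1/(1 − ρ²).
- The minimum detectable difference (MDD) is at 90% power and two-sided 0.05, from the noncentral t. Degrees of freedom are 2n − 3 with age only and 2n − 4 with the arc added. The unit is the SD of ROM given age.

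Every value of ρ below is an assumption.

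| ρ | Variance removed | Sample multiplier | MDD, 31 per arm | MDD, 29 per arm | Fall in MDD |
|---|---|---|---|---|---|
| age only | – | 1.00 | 0.837 | 0.867 | – |
| 0.2 | 4% | 1.04 | 0.820 | 0.849 | about 2% |
| 0.3 | 9% | 1.10 | 0.799 | 0.827 | about 5% |
| 0.4 | 16% | 1.19 | 0.767 | 0.794 | about 8% |
| 0.5 | 25% | 1.33 | 0.725 | 0.751 | about 13% |
| 0.6 | 36% | 1.56 | 0.670 | 0.693 | about 20% |

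Example, ρ = 0.5 with 31 per arm: 1 − 0.25 = 0.75; 1/0.75 = 1.33; 31 × 1.33 ≈ 41 patients per arm for the same precision without the covariate; MDD 0.725/0.837 = 0.87, a fall of about 13%. The table does not include country.

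**3. Why a covariate and not a simple side-to-side difference.** If both sides have the same SD (an assumption), the difference has variance 2(1 − ρ) relative to the raw arc: 1.4 at ρ = 0.3, 1.0 at 0.5, 0.6 at 0.7. Subtraction therefore loses precision below ρ = 0.5. ANCOVA has factors 0.91, 0.75 and 0.51 at the same values and is better at each.

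**4. Timing.** A covariate should not be affected by treatment, so the admission value is preferable. Outcome measures gives no time for the bilateral ROM measurement, whereas the next item there, crepitance, is explicitly scheduled at admission and follow-up. Study procedures states examination of both elbows for follow-up visits only. A bilateral admission measurement is therefore plausible but not stated.

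**The case against.** The strongest case against is that this is an argument from silence. The text says that ROM is handled similarly to the DASH; it does not list the ROM covariates or say that the uninjured side is excluded. The article is condensed, and a full protocol or analysis plan could already assign that measurement a role. An age-adjusted comparison in a randomised trial is valid, so the suggestion is an enhancement to one secondary outcome. Its size rests wholly on an assumed correlation, and motion a year after a fracture also reflects injury and stiffness, so a low correlation cannot be ruled out.

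Much of this stands, and it limits what may be claimed:

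- A reader might infer that the plan throws away the best covariate available. Without an SD or a correlation, nothing shows that it is the best, and no section says that it will be discarded. The accurate statement is that no use is named for it.
- A reader might infer that the other elbow is an intact reference in every patient. Previous contralateral elbow fractures are not clearly excluded, so some may not be normal. That may lower the correlation but does not bias the randomised comparison.

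The objection does not remove the point. Statistical analysis does more than stay silent: it gives ROM a model by reference to the DASH, and applied as written that model adjusts for age alone. The data to improve it are already planned.

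**Conclusion.** The point holds as a low-severity improvement. The stated ROM model names age only, while ROM is collected on both sides and the uninjured side has no stated analytic role.

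A reader might go further and conclude that the ROM comparison is biased, or that the primary result is weakened. The documents do not support either: treatment is randomised, and the DASH analysis and its sample size do not involve this measurement. The only consequence is possible loss of precision on ROM.

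The size depends on a correlation, given age, that the documents do not supply. At an assumed 0.3 to 0.6 the residual variance falls by 9% to 36% and the detectable difference by about 5% to 20%. Below 0.2 the gain in detectable difference is under about 2%, which is negligible.

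**What to change.** Add one sentence to Statistical analysis, fixed before outcome data are seen: flexion arc and rotational arc at one year will each be compared by ANCOVA, with the corresponding arc of the uninjured elbow and age as covariates, and with country because it is a stratification factor.

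State also which uninjured-side value is used. The admission value is preferred if both elbows are measured then, which the sponsor should confirm. Otherwise use the first follow-up value, with the explicit assumption that treatment does not affect the uninjured elbow.

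The cost is one degree of freedom for the uninjured arc and two for country (the Netherlands, the United States and Canada). No new data are needed if both elbows are measured at admission or if the follow-up value is used. Including country follows from the stratification and can be decided separately.

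### The complication count includes arthrosis read only on the one-year film, so degenerative change already present at injury can be counted as a complication and dilute the comparison between arms

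*Protocol article*

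**What the plan says.** **Complications.** In the protocol article, Outcome measures, the number of complications is a secondary outcome. Its components are infection, neurovascular compromise, "subsequent or secondary intervention, arthrosis".

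**Abstract.** Under Methods/Design, the adverse events are infection, nerve injury and secondary interventions. Arthrosis is listed elsewhere, as part of radiographic appearance: "radiocapitellar and ulnohumeral arthrosis, fracture healing, and signs of" implant problems.

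**Grading.** Outcome measures evaluates the joint "on the anteroposterior and lateral radiographs at one year". Degenerative change "will be classified as grade zero (no change), grade 1 (slight narrowing of the" joint space with small osteophytes), and so on up to grade 3. No grade is named as the cut-off for a complication, and no comparison film is named.

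**Films available.** Eligibility rests on plain films: "Diagnosis based on an anteroposterior and lateral radiograph" (Study population). The same section adds: "A CT-scan will be obtained after enrollment/randomization". Study procedures schedules further films: "At the two weeks and twelve months follow-up visit an" AP and lateral pair is made.

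**Who can enter.** Adults of any age from 18. The nearest exclusion to existing joint disease is an earlier fracture of the same elbow. Randomization is stratified by country and by age below 50 against 50 and over (Recruitment and consent).

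**Analysis.** Radiological outcome, conversions and complication rate are each compared by a Fisher exact or chi-square test (Statistical analysis).

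**The concern.** The two component lists give different complication rates from the same data, and the article does not say which governs.

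The longer list also adds a component that differs in kind from the others. Infection, neurovascular compromise and secondary intervention arise after enrolment. Arthrosis graded by appearance at a single time point is a state, and it may have been there before the fracture. The lowest positive grade needs only slight narrowing and small osteophytes. With no upper age limit, a planned stratum of 50 and over and no exclusion for existing arthrosis, some patients may meet that description on the day of injury.

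The complication comparison matters because the Discussion weighs a possible gain in motion from ORIF against a possible excess of complications. A background state that treatment did not cause raises the rate in both arms and makes a real difference between them harder to see. The same reading also enters the radiographic outcome, so one finding contributes to two reported results.

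**Working it through.** **1. The text, side by side.**

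| Item | Outcome measures | Abstract, Methods/Design |
|---|---|---|
| Infection | complication | adverse event |
| Nerve or neurovascular injury | complication | adverse event |
| Secondary intervention | complication | adverse event |
| Arthrosis | complication and radiographic outcome | radiographic outcome only |

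Outcome measures assesses crepitance and block to motion at admission and at every follow-up visit. Radiographic appearance is set at one year only. A baseline reading is therefore stated where it is planned, and none is stated for arthrosis.

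**2. The plan's own figure.** No sample size or power is given for complications. The trial is sized on DASH: effect size 0.85, two-sided alpha 0.05, power 0.90. The noncentral-t solution is 30.08 per group, rounded up to 31 (power 0.909 at 31), so the stated 31 reproduces. I use 31 evaluable per arm below, not the 39 to be enrolled.

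**3. Model.** Let c be the risk of a complication other than arthrosis and q the prevalence of pre-existing arthrosis. Assume that q is equal in both arms and independent of c, and that any such arthrosis is counted.

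- Observed rate: p = c + (1 − c)q.
- Difference: p1 − p2 = (c1 − c2)(1 − q).
- Share of counted patients who are positive only through pre-existing arthrosis: [(1 − c1)q + (1 − c2)q] / (p1 + p2).

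**4. Inputs.** c1 = 44% is the only complication rate in the documents (Background, an earlier ORIF series). Its components are not given, and the article notes that larger screws were used. c2 = 10% is assumed. q is not given, so it is varied from 0 to 30%.

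**5. Results, exact two-sided Fisher test at 0.05, 31 per arm.** Worked example at q = 10%: p1 = 0.44 + 0.56 × 0.10 = 0.496; p2 = 0.10 + 0.90 × 0.10 = 0.190; difference 0.306 = 0.34 × 0.90; share (0.056 + 0.090)/0.686 = 0.21.

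| q | ORIF | Nonoperative | Difference | Power | Share |
|---|---|---|---|---|---|
| 0 | 0.440 | 0.100 | 0.340 | 0.827 | 0 |
| 10% | 0.496 | 0.190 | 0.306 | 0.646 | 21% |
| 20% | 0.552 | 0.280 | 0.272 | 0.501 | 35% |
| 30% | 0.608 | 0.370 | 0.238 | 0.389 | 45% |

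**6. Sensitivity to the assumed nonoperative rate.** At q = 0, 10%, 20% and 30%, power is 0.953, 0.804, 0.638 and 0.501 with c2 = 5%, and 0.433, 0.325, 0.256 and 0.199 with c2 = 20%. The direction is the same each time.

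**7. A low-rate case.** The pooled rates of subsequent surgery in the Background are 5% after ORIF and 2% after nonoperative care. With these as the only complications, the share is 58% at q = 5%, 73% at q = 10% and 85% at q = 20%. Power is 0.002 at q = 0 and stays at or below about 0.03 up to q = 30%, so there is almost none to lose.

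**8. Direction.** If c1 = c2, then p1 = p2 for every q, so equal prevalence creates no difference where none exists. Chance imbalance remains possible: at q = 20%, ignoring stratification, the standard error of the difference in prevalence is √(2 × 0.2 × 0.8/31) = 0.10.

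**The case against.** **Nothing in the text says that any grade on the one-year film is a complication.** The 0–3 scale is given for the radiographic outcome. A complication ordinarily means something that arises after treatment, and an independent, blinded researcher records complications at the last visit. A rule for new versus existing change could sit in the full protocol or analysis plan. This stands in part. The article does not prove that old change will be counted, only that its text allows it, and a missing rule alone would be no finding. What remains is stated text: the component list, the timing of the reading and the conflicting abstract.

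**The label for grade zero suggests a comparison with an earlier film.** The label is ambiguous. Grades 1 to 3 describe absolute appearance, and no earlier film is named.

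**The abstract uses a different term, adverse events, so the mismatch is editorial.** This is fair as far as it goes, but the two lists otherwise cover the same events, and they yield different rates.

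**Randomization takes care of existing arthrosis.** It balances it in expectation, helped by stratification on age. That removes any expected advantage for one arm; it does not remove the dilution.

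**The trial is not powered for complications, and secondary interventions are reported separately.** Both statements are true. They limit the consequence to one secondary outcome, and readers can still see the secondary interventions without arthrosis.

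**Conclusion.** The point holds as a defect in how one secondary outcome is defined. The article gives two component lists that disagree. Under the longer one, degenerative change present at injury can be counted as a complication.

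The expected effect is higher rates in both arms and an absolute difference multiplied by (1 − q). In the illustration, power falls from 0.83 to 0.65, 0.50 and 0.39 at q = 10%, 20% and 30%. This rests on 31 evaluable patients per arm, 44% from an earlier series, an assumed 10%, equal and independent q, and any pre-existing arthrosis being counted. The documents give no prevalence, so these figures show sensitivity and are not a forecast.

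Three stronger readings are not supported:

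- A reader might infer that pre-existing arthrosis would outnumber the real complications. That depends on unknown rates: the share is 73% at q = 10% with 5% and 2%, but stays below half (45%) even at q = 30% with 44% and 10%.
- A reader might infer bias towards one arm. Randomization gives no reason to expect it, although chance imbalance is possible.
- A reader might infer that one year is too short for treatment to cause arthrosis. The documents do not say so.

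The primary DASH analysis is unaffected.

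**What to change.** 1. Make the Outcome measures list agree with the abstract: take arthrosis out of the complication count and keep it as a radiographic outcome. If the investigators prefer to keep it in the count, include only new or worsened arthrosis, state the grade that qualifies, and amend the abstract to match.
2. Grade the diagnostic AP and lateral films on the same 0–3 scale, preferably by the same reader who grades the one-year films. These films are required of every patient and precede treatment in both arms.
3. Report new or worsened arthrosis, meaning a one-year grade above the diagnostic grade.

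The cost is a wording change and a second grading of films that already exist, with no new imaging. The downside is small: joint space is graded less precisely on acute injury films, so some misclassification of change will remain.
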